#### Suspension criteria

• Administration of forbidden medicine.

• Subject's demand to discontinue the study.

• Serious adverse events (AE) or unusual changes in clinical test results.

• Principal investigator's decision to terminate the study (low rates of compliance, complications, or unable to sustain the study for various reasons).

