### Study period

The study period will be of 42 days (total 6 weeks). The visits and the evaluations will be done at the screening (visit1), 0th day (visit2; baseline), 21th day (visit3; 3rd week), and 42nd day (visit4; 6th week). 56th day is a follow up (if needed).

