1.5. Fasting insulin

1.6. Total cholesterol

1.7. Triglyceride

1.8. Low density lipoprotein (LDL) cholesterol

##### Secondary outcome index

1. Diabetes symptoms*

1.1. polydipsia

1.2. polyuria(frequent urination)

1.3. polyphasia

1.4. fatigue

2. Other clinically significant parameters**

3. Anthropometric parameters:

3.1. body weight(kg)***

3.2. waist circumference(WC, cm)

3.3. hip circumference(HC, cm)

The primary and secondary outcomes will be measured at the 0th day (visit2; baseline), the 21th day (visit3; 3rd week), and the 42nd day (visit4; 6th week) during the treating period. And, when necessary, the outcomes will be assessed at the 56th day (follow-up). The changes between the 0th day (visit2; baseline) and the 42nd day (visit4; 6th week) measurements will be analyzed for the primary outcome indexes. For the secondary outcomes, a visual analogue scale (VAS) will be used to detect the improvement of diabetic symptoms (*). When the scale has improved more than two grades or a patient has recovered completely from these symptoms, it will be evaluated as 'effective'. For other categories (**), we will assess whether these parameters have normalized or not. Measured weight minus 0.5 kg (participant's garment weight) will be recorded as the subject's true weight (***).

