### Statistical analyses

#### Efficacy analysis

All analyses in this study will be based on both intention-to-treat (ITT) and per protocol (PP) method. The ITT method will include all randomized subjects who made at least one next visit. The participants who have completed the 6-week treatment without major protocol violations and kept compliance rate over 80% will be analyzed by the pp (per protocol) method. The continuous variables will be summarized as mean±SD (standard deviation) and the categorical variables will be described in frequency and percent. For the primary and secondary outcome variables, the mean differences between before (visit 2; baseline) and after the treatment (visit 4) values will be compared using the paired t-test or Wilcoxon test, in each group. The baseline characteristics will be compared by either the Student t-test for the continuous variables or χ^2^-test for the categorical data (alternatively, Fisher's exact test will be used if the expected value is less than 5 or McNemar's test for non-normal distribution data). The efficacy of PURIAM110 will be assessed by using the independent t-test (when normality assumption is satisfied, alternatively Mann-Whitney test will be used). All analyses will be based on a two-sided test at a 5% significance level. With values of p < 0.05 will be considered statistically significant. SPSS for windows version 12.0 (SPSS Inc., Chicago, Illinois) will be used for analyses. For missing values, 'Last Observation Carried Forward (LOCF)' method will be applied.

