#### Safety analysis

In the safety analysis, it will include the subjects who were both randomized and treated with the investigational drug at least once. There will be stratification by the institution and the adverse event symptom.

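### LOCF puts week-3 values into the week-6 ITT comparison and the ITT set omits subjects with no later visit, so the week-6 difference and SD can be distorted by an unknown amount

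*Protocol article*

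**What the plan says.** The Efficacy analysis section gives one rule for missing data: "For missing values, 'Last Observation Carried Forward (LOCF)' method will be applied". It defines the main analysis set thus: "The ITT method will include all randomized subjects who made at least one next visit". A per-protocol analysis is planned beside it, restricted to six-week completers with compliance above 80% and no major violation.

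The Outcomes section fixes the time point: "The changes between the 0th day (visit2; baseline) and the 42nd day (visit4; 6th week) measurements will be analyzed for the primary outcome indexes". Under Study period and in Table 4, the only scheduled visit between baseline and day 42 is day 21. Day 56 is optional.

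The Suspension criteria foresee early stopping for several reasons, among them "Administration of forbidden medicine" and "Subject's demand to discontinue the study". The Safety analysis uses a wider set than the efficacy analysis: "the subjects who were both randomized and treated with the investigational drug at least once".

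The Objectives and the Discussion say that the pilot is to supply the mean, the SD and the choice of primary endpoint for a larger trial.

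**The concern.** With one visit between baseline and the endpoint, carrying forward nearly always means presenting a day-21 change as a day-42 change. That is harmless only if nothing moves between the two visits, or if any movement is common to both arms and stopping is equal.

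If the effect is still growing at week 3, even equal stopping shrinks the estimated difference. If both arms drift in the same direction, unequal stopping creates a difference where there is none. Stopping may also depend on the outcome. The article does not say that it does, but the suspension criteria include unusual test results, and the laboratory panel contains the primary outcomes.

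The stake is larger than one p-value. The mean difference and SD from this pilot are meant to set the size of the next trial, and carried values enter both as if they had been observed at week 6. With 15 placebo subjects, each one carried or lost is 1/15 = 6.7% of that arm.

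**Working it through.** **The plan's own figure.** 30 + 15 = 45, and 45 × 2/3 = 30, so the total agrees with the 2:1 ratio. The article states no power, effect, SD or dropout rate, so what follows rests on assumptions.

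**What the rules do to each subject**

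| Last efficacy measurement | ITT analysis at day 42 | Per-protocol |
|---|---|---|
| Day 42 | observed value | included if compliant and without major violation |
| Day 21 | day-21 value carried | excluded if the six weeks were not completed |
| Day 0, no later visit | excluded | excluded |
| Day 21 attended, one value missing | baseline could be carried (zero change) | as for day 42 |

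**Assumed inputs.** The unit is the SD of the week-6 change. A share d of an arm stops after week 3, and a share f = 0.5 of the week-6 effect is present at week 3. The SD of change is 0.7 at week 3 and 1.0 at week 6, with correlation 0.6. Each setting was simulated 6,000 times with 30 against 15 subjects and the planned t-test.

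**1. Effect still developing, equal stopping.** Share of the true difference retained = 1 − d(1 − f).
- d = 0.10: 1 − 0.10 × 0.5 = 0.95. Simulated: −0.852 for a true −0.90.
- d = 0.20: 0.90. Simulated: −0.808.
- d = 0.30: 0.85. Simulated: −0.765.

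**2. No effect, shared fall of 1 SD by week 6, unequal stopping.** False difference = 1 × (1 − f) × (d active − d placebo).
- 30% against 10%: 0.5 × 0.20 = +0.10. Simulated +0.106, type I error 6.7%.
- 10% against 30%: −0.10. Simulated −0.100, type I error 5.7%.
- With equal stopping the same trend gave −0.001 and type I error 5.1%.

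**3. Precision (no effect, equal stopping).** With no missing data the SE is √(1/30 + 1/15) = 0.316.

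| Stopping | SE from LOCF t-test | Spread of likelihood week-6 estimate | Ratio |
|---|---|---|---|
| 10% | 0.305 | 0.329 | 0.93 |
| 20% | 0.298 | 0.340 | 0.88 |
| 30% | 0.290 | 0.362 | 0.80 |

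The LOCF figure falls as data are lost. It does match the spread of the LOCF estimator itself (0.298 against 0.296 at 20%), so it is too small only as a statement about the true week-6 effect. If the two SDs are equal, the figures at 20% are 0.315 and 0.347.

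**4. Sizing the next trial.** Within-arm variance under LOCF = (1 − d) × 1.0² + d × 0.7² + d(1 − d)m², where m is the mean movement from week 3 to week 6. Take d = 0.20:
- m = 0: 0.80 + 0.098 = 0.898.
- m = 0.45 (half of 0.90, active arm): 0.898 + 0.16 × 0.2025 = 0.930.

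Required sample size is proportional to variance divided by the squared difference. If the effect is complete at week 3, the ratio to the correct size is 0.898 / 1 = 0.90, about 10% too few. If it is half present, the ratio is 0.898 / 0.81 = 1.11 to 0.930 / 0.81 = 1.15, which is 11 to 15% too many. The direction depends on a timing the article does not give.

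**5. Exclusions.** Losing about 10% before visit 3 leaves roughly 27 against 13, and the SE becomes √(1/27 + 1/13) = 0.338 instead of 0.316.

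**The case against.** The strongest reply is that the harm is modest and assumed. A shift of 0.048 to 0.092 SD at 10 to 20% stopping is 15 to 29% of the complete-data SE of 0.316, and type I error stays close to 5% even with clearly unequal stopping. That stands, and it limits how strongly the point can be put.

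The per-protocol analysis is also a real safeguard, because it already gives a largely unimputed week-6 mean and SD. But it selects on completion, compliance and protocol adherence, all of which arise after randomisation. Agreement between it and the ITT result would not show that carrying forward was harmless.

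A reader might infer four stronger points that the document does not support:
- That confidence intervals will be too narrow. None are planned; the article speaks of means, SDs and p-values.
- That LOCF inflates type I error in itself. With equal stopping and no effect it did not.
- That missingness is known to be informative. The suspension criteria do not say that a forbidden medicine is glucose-lowering or that an unusual test result is glycaemic.
- That subjects who stop are never measured at visit 4. The article is silent, and a condensed article may leave this to the full protocol.

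The name of the ITT set is a matter of terminology, since its definition is disclosed.

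**Conclusion.** The point holds in this limited form. LOCF is a stated rule, not a detail left to an unseen analysis plan. It puts day-21 values into a day-42 comparison, and subjects with no later visit are dropped from the ITT set.

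Bias arises if the effect is still developing at week 3, if a shared trend meets unequal stopping, or if stopping depends on the outcome. Its size and sign cannot be found from the document. The retained 95 to 90%, the false difference of about 0.10 SD in either direction and the sample-size ratios of 0.90 to 1.15 all depend on the assumed dropout, timing and SDs. With no treatment effect and equal, non-informative stopping, LOCF does no visible harm to the test.

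The more certain consequence is for the pilot's second aim: the ITT mean and SD at week 6 would be a blend of two visits. This should be changed, but it does not invalidate the trial.

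**What to change.** For the continuous primary outcomes, replace the LOCF t-test as the main analysis with a likelihood-based repeated-measures model on visits 2, 3 and 4. It should cover all randomised subjects, with baseline included and a treatment-by-visit term. Report the treatment difference at visit 4 and, separately, the SD of the observed visit-4 changes for use in sizing the larger trial. Keep LOCF only as a sensitivity analysis, and keep the per-protocol analysis as planned.

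Under the same assumptions this model had bias near zero, with the larger, honest spread shown above (0.329, 0.340 and 0.362).

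The cost is revised wording and slightly more programming, since visit-3 data are already scheduled. Two limits should be stated in the plan. The model relies on data being missing at random, so it does not fully cure outcome-dependent stopping. Subjects with only a baseline value add very little to the visit-4 contrast. The Study design section says the trial has been running since December 2006, so if results have already been seen by arm, the change should be labelled as made afterwards.

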#### Safety analysis

In the safety analysis, it will include the subjects who were both randomized and treated with the investigational drug at least once. There will be stratification by the institution and the adverse event symptom.

### Adverse event (AE) reporting

All AE must be observed and documented in the CRF AE form. When AE happens, researchers must report it to both IRB and regulatory authorities within 24 hours.

### Data collection

After filling out the CRF, data collection will be performed according to the standard operating procedures (SOPs), by the trained clinical research associates (CRAs).

### Data management and monitoring

For data accuracy and trial quality, monitoring and data management will be carried out by the authorized contract research organization (CRO), Center for Clinical Research and Genomics (CCRG), Seoul, Korea.

### Ethical approvals

The study has been accepted by the Institutional Review Board (IRB) of two hospitals (Institutional Review Board of the Kyung Hee University Oriental Medical Center approved on the 21th of November 2006 (ref: KOMC IRB 2006-14), and Institutional Review Board of the Kyung Won Gil Oriental Medical Hospital approved on the 25th of October 2006(ref: 06-101)). Informed consent form will be provided to each individual prior to the enrolment. The research will be performed in compliance with the Helsinki Declaration and the Good Clinical Practice (GCP) Guidelines.

## Discussion

In this paper, we have suggested the clinical trial design of a pre-diabetes treating dietary supplement. This pilot study will be the groundwork for the larger scale RCT. To draw confirmative conclusion about the therapeutic efficacy and safety of pre-diabetes supplements, a full-scale RCT has to be done. To proceed with the trial, two criteria must be decided through this study. First, the adequate sample size has to be calculated. As there were no published studies with similar outcomes, we had difficulties in obtaining the mean and variation estimates for the study. Therefore, we designed a pilot trial to figure out the mean and standard deviation. Besides, this study result will also provide a magnitude of the clinically significant treatment effect. With these estimates, we will be able to compute the exact sample size of the larger multicenter study. Second, the primary endpoint has to be fixed. The current preclinical study results suggest that bioflavonoids, hesperidin, and naringin, which are contained in mulberry leaves and bitter oranges, prevent not only hyperglycemia but hyperlipidemia in type-2 diabetic animals [17,18,21,22,29,30]. Based on these consequences, we decided to include lipid profile (total cholesterol, triglyceride, LDL cholesterol) indexes, in addition to the glucose related parameters (HbA1c, fructosamine, fasting glucose, 2-h OGTT glucose, fasting insulin). Among the glucose and the lipid related parameters, we will decide the primary outcome for a large scale trial according to the result of this study. Furthermore, as anti-diabetic agents show ethnic differences, PURIAM110 has to be verified by more various groups.

## List of abbreviations used

KNHNS: Korean National Health and Nutrition Survey; IFG: impaired fasting glucose; IGT: impaired glucose tolerance; KFDA: Korea Food & Drug Administration; RCT: Randomized controlled trial; LDL: low density lipoprotein; OGTT: oral glucose tolerance test; WC: waist circumference; HC: hip circumference; VAS: visual analogue scale; SOP: standard operating procedure; QSCC II: Questionnaire for the Sasang Constitution Classification II; ITT: intention-to-treat; PP: per protocol; SD: standard deviation; LOCF: Last Observation Carried Forward; CRF: case report form; AE: adverse event; CRA: clinical research associates; CRO: contract research organization; IRB: Institutional Review Board; GCP: Good Clinical Practice
